### Treatments and therapists

2.5

The clinical trial will randomly assign participants into one of two conditions; 1) iCBT-P, which is the manual developed by Egan et al. (2016) specifically for perfectionism, administered via the Internet, or 2) iUP, which is a transdiagnostic manual intended to target the shared emotional aspects that underlie depression and anxiety disorders, but here adapted to be Internet-delivered. Both treatments will be delivered in a similar manner over eight weeks, consisting of reading material, graphis, audio and video, and a number of exercises to be completed on the secure platform. The key content and main interventions in iCBT-P has been described in the introduction, but broadly involves gaining and understanding of the factors that maintain perfectionism, experimenting with new ways of thinking and behaving, expanding the source for self-evaluation, and managing self-criticism (Shafran et al., 2016), see Table 2 for an overview. Meanwhile, iUP can be regarded as an emotion-focused treatment that intends to raise awareness of the aversive experiences that an individual has a heightened emotional sensitivity for, and which it then tries to alter or avoid (Ellard et al., 2010). Fundamental to iUP is therefore to register and become more aware of the emotions, cognitions, and physical sensations that occur in difficult situation, and to try out more adaptive ways of coping in these instances. Both iCBT-P and iUP relies on techniques that are commonly used in cognitive behavior therapy. However, one crucial difference is that the former emphasizes knowledge acquisition and refuting dysfunctional beliefs to a great degree, such as by testing out predictions in real life, while the latter leans more toward exposure to emotional stimuli and using mindfulness to shift perspectives in relation to thoughts that evoke strong emotions.

**Table 2 t0010:** Treatment content.

Week	iCBT-P	iUP
1	Understanding your perfectionism, e.g., what is unhelpful perfectionism, what are the pros and cons of perfectionism	Emotional symptoms, e.g., what are emotional symptoms, is this treatment for me, registering your experiences, finding your motivation, setting goals
2	Your own model, values, and motivation, e.g., creating an individual conceptualization on what maintains your perfectionism, cost-benefit analysis	Understanding your emotions, e.g., introduction to emotions, what is an emotion, monitor your emotions
3	Surveys and experiments, e.g., introduction to behavioral experiments, pleasurable activities	Emotional awareness, e.g., introduction to emotional awareness, practicing non-judgmental mindfulness, anchoring
4	Dealing with perfectionistic behaviors, e.g., dealing with avoidance and safety behaviors, procrastination, and problem-solving	Thoughts, e.g., what are cognitive judgments, automatic judgments, identifying automatic judgments, thinking errors, cognitive restructuring
5	New ways of thinking, e.g., introduction to cognitive bias, dichotomous thinking, rigidity, focusing on negatives, disregarding positives	Behaviors, e.g., introduction to emotional avoidance, strategies for emotional avoidance, emotional behaviors, preventing avoidance and emotional responses
6	Self-criticism and self-compassion, e.g., introduction to self-compassion, becoming aware of self-critical thinking, practicing compassionate thinking	Emotional exposure, e.g., exposure to emotional situations, imagery, exposure to bodily sensations
7	Self-worth, e.g., introduction to self-worth, becoming less focused on performance, connecting self-worth to values	Continued motional exposure
8	Maintain and continue positive change, e.g., maintaining progress, preventing and managing different setbacks, Q&A, your own plan forward	Planning ahead, e.g., repeating skills and dealing with emotions, determining your progress, becoming your own therapist, long-term goals, maintenance, managing setbacks

iCBT-P = Internet-Based Cognitive Behavior Therapy for Perfectionism: iUP = Internet-based Unified Protocol.

In order to fit with the issues often experienced in perfectionism, a number of slight modifications had to be made to iUP. First, throughout the manual, examples were made perfectionism-relevant from its original focus on depression and anxiety disorders. Second, one module revolves around interoceptive exposure to the physical sensations that often occur in panic disorder, e.g., spinning around on a chair to evoke dizziness. This was considered inappropriate for a study on perfectionism and was therefore removed entirely. The same was also true for a few sections that focused on intrusions and compulsions common in obsessive-compulsive disorder.

Both treatments will be delivered on the secure platform and follow eight separate modules that are delivered as one module per week. Upon randomization, participants are also assigned their own therapist who they can contact when needed, i.e., guidance on demand. This is done via the secure platform, and as soon as a response has been made the participants will be notified once they enter. A message is also sent to their emails, but only to inform that they have to log on to access the response (i.e., no sensitive details are managed outside the secure platform). This approach was used in a previous study (Zetterberg et al., 2019), and did not differ from receiving regular help from a therapist (i.e., scheduled check-ins and feedback twice per week) in terms of outcomes or the number of modules and exercises that were completed. The therapists will consist of students that are either about to complete the study program in psychology (masters degree) who have undergone three semesters of clinical training in cognitive behavior therapy, or the study program in psychotherapy (bachelors degree, i.e., an advanced continuation program focusing specifically on clinical training in cognitive behavior therapy). The therapists respond to questions and provide support on the content and exercises in treatment, but do so freely in their own words. The therapists in the clinical trial will however receive training and supervision from a specialist in iCBT-P and iUP, respectively. Guidance is recorded to keep track of the number of messages sent between the participants and their therapists.

### Ethics and registration

2.6

The clinical trial has received its ethics approval by the Swedish Ethical Review Authority (Dnr: 2020-01868), and has been registered at ClinicalTrials.gov (NCT04459260). Participants will provide informed consent during the recruitment process and screening. Great consideration will also be made to monitor the condition of those undergoing treatment, i.e., deterioration will be flagged automatically by the secure platform and relevant measures will be taken to ensure further help is introduced (see details under statistical analysis). Meanwhile unwanted and adverse events will also be explored after treatment has ended.

### Timeline

2.7

The clinical trial is planned to recruit participants in September 2020. The treatments are expected to be completed in November 2020, with the two follow-up assessments being administered in June and November 2021. A submitted manuscript with the final results is planned to be ready in February 2022.

### Statistical analysis

2.8

In the literature, no prior estimates are available for a power calculation when it comes to what constitutes a reasonable between-group effect size in terms of perfectionism. However, it is reasonable to assume a moderate standardized difference when comparing iCBT-P and iUP on the CPQ in favor of the former. This is based on the assumption that iCBT-P was developed specifically to target perfectionism. Thus, using G*Power to determine the sample size required to detect a Cohen's *d* of 0.50 (α of .05 and β of 0.80) suggest that 64 participants per condition (*n* = 128) will be required for the study. As for the within-group effect size for each condition between screening and post-treatment, the power achieved under these circumstances reveal that it will be possible to detect an effect size *d* of 0.36. The prior study by Zetterberg et al. (2019) demonstrated an effect size *d* of 1.19 on the CPQ for participants receiving iCBT-P with guidance on demand, and > 0.49 for all of the secondary outcomes, which indicates that the current clinical trial should be able to detect a difference on each of the self-report measures.

In terms of the statistical analyses, differences between conditions and between completers and non-completers will be examined using *t*-tests and Pearson *χ*^2^-tests. Conditional changes over time on both the CPQ and PHQ-9 will be modeled using an intention-to-treat linear mixed-effect model using data from screening, weekly assessment, and post-treatment assessment, and employing random slops, unstructured covariance matrix, and full maximum likelihood estimation with 100 iterations. The other self-report measures have fewer data points and are therefore considered inappropriate for mixed-effects modeling (Hesser, 2015). These will therefore be analyzed using repeated measures analysis of variance and using multiple imputation to deal with missing data. Effect sizes *d* will be calculated to determine the standardized differences in means within and between conditions, and 95% Confidence Intervals will be reported. Clinically significant change, criterion A, will be used to identify the number of participants who have recovered in their perfectionism. As perfectionism is not a diagnosis, recovery will be defined as reaching a statistical criterion of two standard deviations of change from the mean in the direction of a functional distribution on the CPQ, and exceeding measurement error as defined by the reliable change index (Jacobson and Truax, 1991). The latter will also be utilized to determine the number of participants who have experienced non-response and reliable deterioration (Rozental et al., 2014a).

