### Self-report measures

2.4

The clinical trial will include two main outcomes concerning the levels of perfectionism among the participants; the Clinical Perfectionism Questionnaire (CPQ; Fairburn et al., 2003), and the FMPS (Frost et al., 1990). The CPQ consists of 12 items that are scored on a four-point Likert-scale 1–4 (“Not at all” to “All of the time”), with two items that are in reverse (items 2 and 8), and employing a time-frame of one month to increase its clinical usefulness. The CPQ was translated to Swedish in a previous clinical trial, demonstrating good convergent and discriminant validity when compared to self-report measures of perfectionism and psychiatric symptoms, as well as adequate internal consistency (α = .68) and test-retest reliability (*r* = .62) (McMahan et al., submitted). The FMPS is scored on a five-point Likert-scale 1–5 (“Strongly disagree” to “Strongly agree”), with a total of 35 items that cover the six separate subscales Concern over Mistakes, Personal Standards, Doubts about Action, Parental Expectations, Parental Criticism, and Organization. However, only the first two are usually of interest in clinical trials as the other subscales are considered less related to the two higher-order dimensions of perfectionism (Limburg et al., 2017). The subscales of the FMPS has adequate to excellent internal consistencies (.88 and .83) and exhibits convergent and discriminant validity when compared to self-report measures of perfectionism and psychiatric symptoms (Purdon et al., 1999). The FMPS was originally translated to Swedish by Lundh et al. (1994). Apart from completing the two main outcomes during screening and at post-treatment and follow-up, participants will also fill out the CPQ weekly during treatment, see Table 1 for an overview.

**Table 1 t0005:** Overview of the self-report measures.

Self-report measure	Assessment											
	Screening	1	2	3	4	5	6	7	8	Post	6 months	12 months
CPQ	X	X	X	X	X	X	X	X	X	X	X	X
FMPS	X									X	X	X
PHQ-9	X	X	X	X	X	X	X	X	X	X	X	X
GAD-7	X									X	X	X
BBQ	X									X	X	X
SCS-SF	X									X	X	X
PPS	X									X	X	X
PSS	X									X	X	X
Credibility			X									
Domains^a^	X									X	X	X
Goals^b^	X									X	X	X
NEQ										X		

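### The FMPS and the other non-weekly scales are compared between arms by repeated measures ANOVA, which uses the screening score less efficiently than adjusting for it would

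*Protocol article*

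**What the plan says.** Section 2.4 and Table 1 of the protocol article show that both main outcomes, the CPQ and the FMPS, are measured at screening, post-treatment, 6 and 12 months. Most secondary scales follow the same schedule. Only the CPQ and PHQ-9 are also measured weekly. Section 2.1 describes 1:1 allocation from a random numbers generator and mentions no stratification by score.

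Section 2.8 names two between-arm analyses and one effect size:

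- CPQ and PHQ-9: an intention-to-treat "linear mixed-effect model using data from screening, weekly assessment, and post-treatment assessment", with random slopes.
- All other self-report measures, including the FMPS: "These will therefore be analyzed using repeated measures analysis of variance and using multiple imputation to deal with missing data".
- Effect sizes d that "will be calculated to determine the standardized differences in means within and between conditions", with 95% confidence intervals.

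The section does not name the screening score as a covariate, and it does not state a common screening mean for the two arms.

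**The concern.** Any arm difference at screening arises by chance. Repeated measures ANOVA nevertheless gives each arm its own screening mean and compares the change from it. That subtracts the whole screening difference, although only a fraction of it (the regression slope of post-treatment on screening) is expected to persist. Two consequences follow: the interval is wider than it need be at the same sample size, and in a trial that happens to be imbalanced the estimate is pushed in the direction opposite to the imbalance.

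The choice is written into section 2.8 for one of the two main outcomes, so an analysis plan that followed the section would carry it forward. The between-arm contrast is also the one that the trial is sized on.

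**Working it through.** **Inputs from the document.** Between-arm d = 0.50 on the CPQ, and "α of .05 and β of 0.80) suggest that 64 participants per condition" (section 2.8). The 0.80 only works as power. No screening-to-post correlation r is given for any scale. The nearest figure is for the CPQ: section 2.4 reports it "as well as adequate internal consistency (α = .68) and test-retest reliability" of .62. Using .62 as r is an assumption, and it is a larger one for the FMPS, so a range is shown.

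**Reproducing the plan's sample size.** A two-sample t-test (noncentral t, two-sided 0.05, d = 0.50) needs 64 per arm, with power 0.801. The stated figure reproduces as an unadjusted two-group comparison.

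**Screening-to-post contrast in the ANOVA.** With two occasions, the arm-by-time test is the t-test on post minus screening. With unit SD at both occasions, the variances per participant are:

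- change score: 2(1 − r)
- adjusted for screening: 1 − r²
- ratio: 2(1 − r)/(1 − r²) = 2/(1 + r), which exceeds 1 for every r below 1

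Power at 64 per arm, with d = 0.50 divided by the square root of each variance:

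| r (assumed) | change variance | adjusted variance | ratio | power, change | power, adjusted |
|---|---|---|---|---|---|
| 0.30 | 1.40 | 0.910 | 1.54 | 0.660 | 0.837 |
| 0.40 | 1.20 | 0.840 | 1.43 | 0.727 | 0.865 |
| 0.50 | 1.00 | 0.750 | 1.33 | 0.801 | 0.900 |
| 0.62 | 0.76 | 0.616 | 1.23 | 0.896 | 0.947 |
| 0.68 | 0.64 | 0.538 | 1.19 | 0.939 | 0.969 |

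**Unequal SDs.** Let the post-treatment SD be 1 and the screening SD 1/k. The change variance becomes 1 + 1/k² − 2r/k, and the adjusted variance stays at 1 − r². At r = 0.62:

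- k = 1.15 (assumed): 0.678 against 0.616, power 0.926 vs 0.947
- k = 1.3 (assumed): 0.638 against 0.616, a ratio of 1.036, power 0.940 vs 0.947

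A k above 1 is plausible for Concern over Mistakes, because section 2.2 admits only scores above 29 at screening.

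**Chance imbalance.** The SD of the screening difference between arms is √(2/64) = 0.177 SD units. With equal SDs, an imbalance of 0.2 SD moves the change-score difference by −0.2(1 − r). That is −0.12 at r = 0.4 and −0.076 at r = 0.62. Adjustment removes this in expectation.

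**CPQ and PHQ-9 mixed model.** Take 10 equally spaced occasions, screening variance 1 split .62 between persons and .38 residual, and a random-slope SD of 0.5 to 0.9 over the period (all assumed). Compare the GLS variance of the slope difference with the arms free at screening and with a common screening mean. For intercept-slope correlations from −0.4 to 0.2, the common mean cuts that variance by 0 to 25%. The large cuts occur at negative correlations. At slope SD 0.7 and correlation −0.4 the SE falls from 0.164 to 0.142, but that setting implies a screening-to-post correlation of only 0.39. Settings under the same split that imply about 0.62 (slope SD 0.5 with correlation 0.4, or slope SD 0.7 with 0.47) show a cut below 1%.

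**The case against.** The strongest reply is that nothing here is invalid. Under randomisation a change-score comparison is unbiased on average and keeps its type I error. The imbalance argument is conditional on the imbalance that happens to occur. This stands, and it makes the point one of precision.

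A second reply is that an article leaves model detail to an analysis plan. This also stands for the mixed model. A reader might infer that the CPQ and PHQ-9 model lets the arms differ freely at screening, but section 2.8 does not say so. No wrong choice is shown there, and the gain from a common mean may be close to nil. The reply does not reach the FMPS, because repeated measures ANOVA is itself the stated method.

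A reader might also infer that the between-arm d comes from raw post-treatment means. The article says only that it is a standardised difference in means, which could be model-based or adjusted. For the same reason, the gap between 0.801 and 0.947 at r = 0.62 (14.6 points) should not be cited as the gain. The post-only test is the sizing calculation, and neither planned analysis uses it. The relevant comparator is change, a gap of 5.1 points at that r.

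Finally, sections 1.2 and 3 disclaim a superiority design, and the first two research questions concern each treatment separately. That lowers the stakes of the between-arm estimate but does not remove them, since section 2.8 sizes the trial on that estimate.

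**Conclusion.** The point holds as an available gain in precision, most firmly for the FMPS and the other scales analysed by repeated measures ANOVA. With equal SDs, the screening-to-post change comparison has a variance 19% to 54% above the adjusted one for r from 0.68 down to 0.30. At r = 0.62 the excess is 23%, and it falls to about 4% if the post-treatment SD is 1.3 times the screening SD. All of these rest on an assumed r, because the document gives no FMPS correlation and only a test-retest value for the CPQ.

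It would be too strong to say that the planned 80% power is undercut. With equal SDs that happens to the change comparison only if r is below about 0.5, and the one figure in the document, .62, lies above this. For the CPQ and PHQ-9 the size of any gain cannot be determined from the document.

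**What to change.** In section 2.8:

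1. For the FMPS and the other scales measured at screening and follow-up, estimate the between-arm difference at post-treatment, 6 and 12 months from a model with that measure's own screening score as covariate.
2. Base the between-condition d and its 95% confidence interval on this adjusted difference, and name the standardising SD in advance. The within-condition d can stay as planned.
3. For the CPQ and PHQ-9 mixed model, keep screening as a response and constrain the two arms to a common mean at screening. Moving screening to a covariate main effect is not equivalent in a random-slope model. It would also need a covariate-by-time term to adjust the slope difference.

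The cost is a few lines of wording and one degree of freedom for each covariate. No new data, visits or participants are needed.

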### Qualitative interviews

2.9

Following the post-treatment assessment, participants will be asked to be part of a qualitative interview that intends to investigate their experiences of undergoing treatment and its impact. In total, 12 participants from each condition will be recruited (*n* = 24), based on their results: recovery, non-response, and deterioration, as defined above. The interviews will be conducted via telephone and follow a semi-structured and open format.

## Discussion

3

The present study protocol has described and outlined clinical trial that will compare two forms of cognitive behavior therapy delivered via the Internet; iCBT-P, specifically developed for treating perfectionism, and iUP, a transdiagnostic treatment for the emotional aspects that are believed to be an underlying process involved in depression and anxiety disorders. Both of the treatments will be delivered over the course of eight weeks and with guidance on demand. The clinical trial will first and foremost replicate prior findings concerning the benefits of cognitive behavior therapy for perfectionism and psychiatric symptoms (Rozental et al., 2017; Shafran et al., 2017; Zetterberg et al., 2019), but it will also be the first study where this treatment is compared to an active comparison condition. In addition, the two treatments make it possible to study their specificity in terms of outcomes, that is, to what extent each seem to have a positive impact on perfectionism and psychiatric symptoms, respectively. Although the clinical trial is not designed to test, for instance, superiority, iCBT-P is nonetheless expected to have a greater impact on perfectionism given that it was developed specifically for its treatment. The results from the study will be able to provide information that can be used for future studies on this issue. Furthermore, the self-report measures being used will allow an exploration of the effects on not only levels of perfectionism, but also psychiatric symptoms, self-compassion, and quality of life up to 12 months following treatment. Likewise, using a qualitative interview will make it possible to investigate the experiences of undergoing treatment of perfectionism via the Internet and the impact it might have on the participants.

The clinical trial has several strengths that should be discussed. Both of the principal investigators (MB and AR) as well as all of the researchers involved have extensive experiences of conducting studies on Internet-based cognitive behavior therapy, and the secure platform has been used in a large number of clinical trials (Vlaescu et al., 2016). Thus, this will guarantee an efficient recruitment period and administration of the treatments and self-report measures. Both iCBT-P and iUP have also received empirical support for their use and should therefore produce benefits for the participants receiving them. In addition, weekly assessments of perfectionism and depression improves statistical power and allows more advanced statistical modeling. However, there are also a number of limitations that should be addressed. Because perfectionism is not considered a diagnosis, determining who is eligible for treatment and who has recovered are complicated issues. Using a statistical criterion like the one that has been proposed is not uncommon in the absence of clear cutoffs, e.g., procrastination (Rozental et al., 2015). Nonetheless, other methods should be used to assess whether someone can be included and if recovery has in fact occurred. The clinical trial will therefore incorporate a number of additional ratings that can help to examine this, such as to what extent the participants think their perfectionism is affecting them negatively on various dimensions prior to initiating and after treatment, e.g., friendships/social life, and whether the goals of treatment has been accomplished or not. Qualitative interviews will also be conducted to explore the participants' experiences of the treatments and to what extent they have made an impact, similar to Rozental et al. (2020). Moreover, using self-referrals in clinical trials can be problematic as they do not always reflect the demographic composition of the general public. Whether this is true also for individuals having difficulties due to perfectionism is unclear, but should be explored by probing how they were recruited and to make an effort in advertising the study on multiple locations and through different media. Lastly, although adherence to treatment can be registered in terms of number of completed modules, determining how much time each participant spend on reading the content and doing the exercises is difficult to assess. The clinical trial will probe for this using open ended questions and self-reports, but a closer and more detailed inspection would have been preferred to explore dose-response issues.
